
##### Recent Physical Activity Questionnaire (RPAQ)

Self-reported physical activity is measured using the RPAQ. This assesses physical activity across four domains (domestic, recreational, work, commuting) over the previous month. It has shown moderate-to-high reliability for physical activity energy expenditure and good validity for ranking individuals according to their time spent in vigorous intensity physical activity and overall physical activity energy expenditure [57].

##### Health-related quality of life (HRQL)

HRQL will be measured by the SF Community - short-form survey (SF*-*12™) Colombian version for physical and mental domains’ summary scores and eight subscales (including vitality) [58]. The internal consistency of the HRQL items is moderate (Cronbach’s alpha = 0.70).

##### Sociodemographic information

Baseline sociodemographic values, which could act as covariates or confounds for the tested treatment modality, will also be collected. The surveys will include questions on age, education, occupation, income, health history, and alcohol consumption, among others.

##### Dietary assessment

To determine the average habitual energy and macronutrient intake, a detailed 24-h diet record will be obtained from all subjects 1 weekday and 1 weekend day during the 1-week baseline period. The Food Intake Analysis Software (FAO/INFOODS, Report of the Technical Workshop on Standards for Food Composition Data Interchange, Rome 2004) and national food composition tables (for specific foods) will be used to analyse total energy and macronutrient intake of each subject’s 24-h diet.

##### Side effects and monitoring

The study will be conducted according to good clinical practice and standard operating procedures. It will be monitored by the Human Rights Committee at the Universidad Manuela Beltrán Coordinating Centre composed of experts in physical exercise, sports medicine, physical therapists, physical educators and clinical epidemiologists. Interim monitoring reports will be submitted to the experts, focusing on patient intake, adherence to the protocol, baseline comparability of treatment groups, completeness of data retrieval, and adverse events. All adverse events will also be reported to the Universidad Manuela Beltrán Ethics Committee. To standardise the study procedures, an operations manual has been written, and comprehensive training sessions will be held prior to the initiation of the trial. An independent researcher will be in charge of auditing all assessment staff to record all of these events for the participants over the study period.

### Power calculation and sample size

The aim of this study is to obtain data on the effects of HIIT, RT or combined training that will result in similar improvements in cardiometabolic health compared to the usual clinical care group. The measurement of FMD, validated in several population studies, was selected as the critical variable to calculate the sample size [59, 60]. To calculate the required sample size, we will use the formula for the comparison of two means:$$ n={\left[A+B\right]}^2\times 2\times S{D}^2/DIF{F}^2, $$ where *n* = the sample size required in each group, *SD* = standard deviation of the outcome variable, and *DIFF* = size of desired difference between groups. *A* and *B* depend on the desired significance level and desired power, respectively. Using estimates obtained from the literature [59, 60] and our previously performed study [61, 62], a sample size of 12 subjects in each group will be needed to reach a power of 80 % to detect a difference in means in the FMD of 2 % in the FMD after 12 weeks of training, assuming a SD of 2.7 using a two-sample *t* test with a 0.05 two-sided significance level. Assuming a drop-out rate of 15 %, the total minimal sample size has been increased to 15 subjects for each group. We believe that this sample size is feasible and realistic based on our previous experiences in RCTs [33, 34, 59, 60, 63, 64].

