Thus, this paper describes the rationale, design, and methodologies used in a factorial randomised controlled trial (Cardiometabolic HIIT-RT Study), wherein we hypothesised that HIIT and combined training would result in greater improvements in vascular function compared to RT and usual clinical care.

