#### Statistical analyses

The final data will be analysed using IBM SPSS 22.0 (SPSS, Inc., Chicago, IL, USA) and SAS software (SAS Institute Inc., Cary, NC, USA). An exploratory analysis will be performed to determine the frequency, range, variability, and distribution type for each variable to use the most appropriate statistical test when comparisons will be necessary. These analyses permit the assessment of the primary analysis of the data and will be undertaken using the principle of intention-to-treat (ITT). The ITT analysis for this study will include all participants, including those who are not fully compliant and those with missing outcome data. Because this is an experimental design with two measures of the primary and secondary outcomes, the first at baseline x0 (t0 = weeks) and the second after interventions x1 (t1 = 12 weeks) in four study groups, a comparative analysis between these measures to establish differences will be executed. To perform these comparisons, one-way ANOVA or Kruskal-Wallis tests will be applied when appropriate. Subsequently, a multivariate analysis will be carried out, and the autocorrelation between repeated measures will be taken into account. We will use longitudinal analysis methods, such as a generalised estimating equation approach, to control the differences among measures at baseline and to incorporate incomplete observations into this analysis. Finally, we will investigate if there is an interaction between the two interventions for the primary outcome at 12 weeks of supervised training HIIT, RT or combined training (HIIT + RT). For these analyses, we will include appropriate interaction terms in the models [38, 65]. The trial is not powered to detect these interactions and is likely to have poor precision for the interaction terms. We plan to report regression coefficients for the interaction terms and their 95 % confidence intervals. However, we aim to recruit 15 participants per group (a total of 60) to accommodate for a 20 % attrition rate and elimination due to non-compliance.

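### The sample-size section states an aim of similarity to usual care, against a superiority hypothesis and a design with no equivalence margin; the omnibus ANOVA does not target that hypothesis either

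*Protocol article*

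**What the plan says.** The Background gives the hypothesis as directional: "HIIT and combined training would result in greater improvements in vascular function compared to RT and usual clinical care". Study design and setting calls the trial a 2 × 2 factorial, so the four arms are usual care, RT alone, HIIT alone, and both.

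Power calculation and sample size begins with a different aim, which it words in terms of "HIIT, RT or combined training that will result in similar improvements in cardiometabolic health compared to the usual clinical care group". What follows in that section is a calculation for finding a difference. It uses the two-means formula, in which DIFF is the "size of desired difference between groups". The requirement is put this way: "a sample size of 12 subjects in each group will be needed to reach a power of 80" per cent. The purpose given for that number is "to detect a difference in means in the FMD of 2 % in the FMD after 12 weeks of training", and the calculation assumes an SD of 2.7 and a "0.05 two-sided significance level".

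Statistical analyses says that, for the four-group comparison, "one-way ANOVA or Kruskal-Wallis tests will be applied when appropriate". It then adds longitudinal models that control for baseline, and models with interaction terms reported with 95% intervals. Neither section contains an equivalence or non-inferiority margin.

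**The concern.** The aim attached to the sample size should say what the trial is sized to show. Here it says the training arms will improve about as much as usual care, whereas the Background says two of them will improve more. Both cannot be the aim for the same comparator. The practical risk lies in interpretation. A reader holding only the sample-size section could take a non-significant difference as agreeing with the aim, although nothing in the design allows similarity to be shown.

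A second mismatch concerns the test. The hypothesis sets the two arms containing HIIT against the two without it. A four-group omnibus test spreads its three degrees of freedom over every possible pattern of differences, and a significant result does not say which pattern was found.

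**Working it through.** **Inputs.** Difference 2 FMD points, SD 2.7, two-sided 0.05, 12 per arm (15 after allowing for drop-out), all from Power calculation and sample size. The four-arm factorial layout is from Study design and setting.

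**1. The plan's own figure.** n = (A + B)² × 2 × SD² / DIFF² = (1.960 + 0.842)² × 2 × 2.7² / 2² = 28.6, so 29 per arm (30 by the exact t calculation), not 12. This is a separate error. It matters here only because the formula is plainly one for detecting a difference.

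**2. The statements side by side.**

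| Place | Claim or method | Type |
|---|---|---|
| Background | HIIT and combined better than RT and usual care | Superiority |
| Power section, opening sentence | Training arms similar to usual care | Similarity |
| Power section, calculation | Detect 2 points, two-sided 0.05 | Difference |
| Statistical analyses | ANOVA or Kruskal-Wallis, regression models | Difference |

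The opening sentence is the only one that points to similarity, and it has no margin behind it.

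**3. Could a null result support similarity?** For two arms of n, the 95% half-width is h = t(0.975; 2n − 2) × 2.7 × √(2/n).

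- n = 12: 2.074 × 1.102 = 2.29 points.
- n = 15: 2.048 × 0.986 = 2.02 points.

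Even an observed difference of exactly zero would leave the 2-point target inside the interval.

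Baseline adjustment would narrow this by √(1 − r²), but the document states no baseline correlation r. As an assumed range:

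- r = 0.5 (factor 0.866): 2.29 × 0.866 = 1.98 and 2.02 × 0.866 = 1.75.
- r = 0.8 (factor 0.6): 2.29 × 0.6 = 1.37 and 2.02 × 0.6 = 1.21.

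A non-significant estimate can lie anywhere up to h from zero, so its interval can reach nearly 2h. At r = 0.8 that is 2 × 1.37 = 2.74 and 2 × 1.21 = 2.42, still beyond 2 points. Non-significance alone therefore cannot establish similarity within 2 points anywhere in this range. The 2-point yardstick is the plan's superiority target, borrowed here because no margin is given.

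**4. Omnibus test against the HIIT margin.** Assume HIIT adds 2 points, RT adds nothing and there is no interaction, so the means are 0, 0, 2, 2. The omnibus F has noncentrality n × 4 / 2.7² on 3 and 4n − 4 degrees of freedom. The margin contrast has standard error 2.7 × √(1/n).

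| Per arm | Noncentrality | Omnibus F power | Margin contrast power |
|---|---|---|---|
| 12 | 6.58 | 52% | 71% |
| 15 | 8.23 | 63% | 80% |

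For this pattern the contrast gains 19 points at 12 per arm (71 − 52) and 17 at 15 (80 − 63), with no extra participants.

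**5. Limit of the margin.** Take assumed gains of usual care 0, RT 2, HIIT 2 and combined 4. The margin is (2 + 4)/2 − (0 + 2)/2 = 2 points, yet HIIT does not exceed RT, so the Background hypothesis fails. The margin alone does not establish that hypothesis.

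**The case against.** The best defence is that this is one badly chosen word with no operative role. Every working part of the plan tests for a difference, and the Abstract and Discussion also speak of effectiveness and of which programme is better. The sentence might also have meant that the three training modes improve similarly to one another, each judged against usual care. That is plausible, and a drafting slip is the likeliest explanation. It does not rescue the text: read literally the sentence contradicts the Background, and the kinder reading still clashes with it on HIIT against RT.

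A reader might infer that the protocol would count a null result as success. The documents do not support that; they contain no such rule, so the misreading is a risk and not a plan.

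A reader might also take low power for the two-arm comparison (41% at 12 per arm, 50% at 15) as the size of this point. It is not. That shortfall comes from the separate sample-size error, and rewording the aim would not change it.

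Finally, the choice of a primary contrast is often left to an analysis plan, and Statistical analyses does go on to baseline-controlled and interaction models. That stands as far as it goes. The point on the test is therefore not that detail is missing, but that the test the protocol does name for the group comparison is not aimed at its own hypothesis.

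**Conclusion.** The point holds as a contradiction in the stated aim, joined to a poorly targeted test. The similarity aim conflicts with the Background hypothesis and with the section's own calculation. It has no margin, and a two-arm interval of ±2.3 points (12 per arm) or ±2.0 (15 per arm) means non-significance could not bear it out. Those widths take 2.7 as the unadjusted SD of the outcome, as the protocol defines it; adjustment would narrow them by an amount the document does not allow one to fix.

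The power advantage of the margin contrast over the omnibus test rests on no RT effect and no interaction, and would differ under other patterns. It is tempting to equate the Background hypothesis with the HIIT main effect, but the documents do not support this: the hypothesis also implies that HIIT alone exceeds RT alone, which the margin averages over.

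The correction is worth making because it is cheap and settles what the trial claims to test. It does not bear on the validity of the randomisation or of the endpoint.

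**What to change.** In Power calculation and sample size, replace the similarity sentence with the superiority hypothesis from the Background.

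In Statistical analyses, test that hypothesis with pre-specified contrasts on week-12 FMD adjusted for baseline, in place of reliance on the omnibus ANOVA:

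- the factorial HIIT margin: HIIT and HIIT + RT against RT and usual care;
- the HIIT × RT interaction with its 95% interval, as already planned;
- the arm comparisons as supporting contrasts, including HIIT against RT, which the margin alone does not establish.

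A short statement that a non-significant difference will not be read as similarity would close off the misreading.

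The cost is a change of wording and of the named test, with no added recruitment. The downside is that the margin averages over RT and is harder to interpret if there is an interaction. The section must also say which comparison its sample size refers to, since the present calculation is for two arms. The figure of 12 per arm needs its own correction; this change does not repair it.

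### The stated 12 per group does not follow from the protocol's own formula and inputs, which give 29, so the 80 % power claim for FMD is unsupported as printed

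*Protocol article*

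**What the plan says.** In the Power calculation and sample size section, the authors write that "we will use the formula for the comparison of two means". They print n = [A+B]² × 2 × SD²/DIFF² and define n as "the sample size required in each group". A and B are the terms for significance level and power, SD is that of the outcome variable, and DIFF is the between-group difference sought.

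The result follows: "a sample size of 12 subjects in each group will be needed to reach a power of 80" per cent. The target is "to detect a difference in means in the FMD of 2" per cent after 12 weeks, "assuming a SD of 2.7 using a two-sample *t* test with a 0.05 two-sided significance level". The inputs are attributed to the literature and to the group's own earlier work.

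The section then allows for losses: "Assuming a drop-out rate of 15 %, the total minimal sample size has been increased to 15 subjects for each group". The Statistical analyses section gives another allowance for the same number: "we aim to recruit 15 participants per group (a total of 60) to accommodate for a 20 % attrition rate", where the sentence goes on to include removal for non-compliance.

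**The concern.** Every input to the calculation is printed, so the stated result can be checked directly, and it does not reproduce. FMD is the primary outcome, and this calculation is the only statistical justification given for the trial's size: 15 per group and 60 in total are both built on 12.

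The consequence is for interpretation. A reader who accepts 80 % power could take a non-significant pairwise comparison as good evidence against a 2-point effect. If the printed SD and difference are right, it would be no such thing. The section's opening aim, which speaks of similar improvements, makes that misreading easier.

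**Working it through.** **Inputs**, all from Power calculation and sample size: DIFF = 2 FMD points; SD = 2.7; two-sided alpha 0.05, so A = 1.960; power 80 %, so B = 0.842; n counted per group.

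**The printed formula**

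- [A+B]² = (1.960 + 0.842)² = 7.85
- n = 7.85 × 2 × 2.7² / 2² = 7.85 × 2 × 7.29 / 4 = 28.6, rounded up to **29 per group**
- Exact two-sample t test (noncentral t, 2n − 2 degrees of freedom): **30 per group**
- Stated: **12 per group**

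**Power of the stated test with SD 2.7 and difference 2**

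The noncentrality is DIFF / (SD × √(2/n)).

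| Evaluable per group | Noncentrality | Power, exact t | Power, normal approximation | Difference detectable at 80 %, exact t |
|---|---|---|---|---|
| 12 | 2 / (2.7 × √(2/12)) = 1.81 | 41 % | 44 % | 3.2 points |
| 15 | 2 / (2.7 × √(2/15)) = 2.03 | 50 % | 53 % | 2.9 points |

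The choice of method does not alter the conclusion.

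**Which inputs would give 12?**

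- *Smaller SD, all else unchanged.* Solving the formula at n = 12: SD = 2 × √(12/2) / 2.802 = 1.75. An SD of 1.7 gives 7.85 × 2 × 1.7² / 4 = 11.3, so 12 (exact t power 79 %).
- *Larger difference, all else unchanged.* DIFF = 2.7 × 2.802 × √(2/12) = 3.1.
- *Factor 2 omitted and one-sided alpha.* This gives 11.3, so 12, but contradicts both the printed formula and the two-sided test.
- *One-sided paired t test.* This gives 13, which is close, but again is not the stated test.

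Several routes lead to 12 or near it, and the article does not show which, if any, was taken.

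**Baseline adjustment**

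Adjusting for baseline with correlation ρ multiplies the required n by 1 − ρ². To bring 28.6 down to 12, ρ = √(1 − 12/28.6) = 0.76. The exact t calculation asks for slightly more. The article states no such correlation.

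**Loss allowance**

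12 / 0.85 = 14.1, so 15; 12 / 0.80 = 15. Both percentages lead to 15 per group.

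**The case against.** The strongest objection is that the inconsistency does not show which number is wrong. The SD and the difference come from cited sources that are not at hand. A single-digit slip (2.7 for 1.7) would explain 12 with the formula and the two-sided test intact. This stands. A reader might infer that the trial's true power is 41 %, or that the authors dropped the factor 2 and used a one-sided test. The article supports neither as fact: the 41 % is conditional on the printed SD and difference, and the origin of 12 is unknown.

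Second, 41 % belongs to an unadjusted t test. The Statistical analyses section plans one-way ANOVA or Kruskal-Wallis, then longitudinal models such as generalised estimating equations that account for baseline. Adjustment would raise power: with assumed correlations of 0.5, 0.6 and 0.7, 12 per group gives about 52 %, 58 % and 68 %. This also stands, but it does not rescue the claim. The sample size section uses the SD of the outcome and an unadjusted test, with no correlation. The intra-class correlation of 0.83 reported for FMD under Endothelial function is reliability from repeated baseline measurements in 8 subjects, not a correlation over 12 weeks of intervention.

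Third, the trial is described as 2 × 2 factorial, so pooling arms might seem to supply the missing power. The calculation is written for two groups with n in each, and no pooling enters it. Even at the margins, 12 per arm gives 24 v 24 and about 71 % power; 30 v 30, with nobody lost, gives 80.5 %. Which contrast should carry the trial is a design choice that this arithmetic does not settle.

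Finally, the 15 % and 20 % may describe different things, since the second also covers removal for non-compliance. As both lead to 15, the mismatch has no numerical effect.

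**Conclusion.** The point holds as an arithmetic contradiction. The printed formula and inputs require 29 per group (30 by the exact t test), and the article states 12, about 40 % of that (12/29). Nothing elsewhere in the article repairs it. The acknowledgement of low power in Statistical analyses concerns interaction terms only and leaves the 80 % claim for the primary outcome unqualified.

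The size of the shortfall is conditional. If SD 2.7 and a difference of 2 are intended, and the test is the unadjusted one named, power is about 41 % with 12 evaluable per group and 50 % with 15. It would be tempting to say that the trial would miss a true 2-point difference more often than find it. That fits 12 per group under these assumptions, but at 15 the odds are about even, and an adjusted analysis would do better by an amount the article gives no means to fix. The loss-figure discrepancy is a minor point of consistency.

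**What to change.** No further enrolment is needed.

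1. Check the SD and the difference against the sources from which they were taken. An SD of about 1.7 or a difference of about 3.1 would reproduce 12. Correct whichever printed figure is wrong.
2. If 2.7 and 2 both stand, replace the 80 % claim. Suggested wording: *With an SD of 2.7, the formula requires 29 per group for 80 % power to detect a 2-point difference in FMD. An unadjusted two-sample t test has about 41 % power with 12 evaluable participants per group and 50 % with 15; the pairwise difference detectable with 80 % power is about 3.2 or 2.9 points respectively.*
3. In that case, present pairwise comparisons as estimates with 95 % confidence intervals, so that a null result is not read as excluding a 2-point effect.
4. If credit is taken for baseline adjustment, state the assumed baseline-to-follow-up correlation and its source.
5. Use one loss figure throughout, or explain that 15 % and 20 % cover different losses.

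The cost is a look at the sources and a few sentences of protocol and analysis-plan wording. If the printed inputs are confirmed, the stated pairwise power becomes less favourable.

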#### Statistical analyses

The final data will be analysed using IBM SPSS 22.0 (SPSS, Inc., Chicago, IL, USA) and SAS software (SAS Institute Inc., Cary, NC, USA). An exploratory analysis will be performed to determine the frequency, range, variability, and distribution type for each variable to use the most appropriate statistical test when comparisons will be necessary. These analyses permit the assessment of the primary analysis of the data and will be undertaken using the principle of intention-to-treat (ITT). The ITT analysis for this study will include all participants, including those who are not fully compliant and those with missing outcome data. Because this is an experimental design with two measures of the primary and secondary outcomes, the first at baseline x0 (t0 = weeks) and the second after interventions x1 (t1 = 12 weeks) in four study groups, a comparative analysis between these measures to establish differences will be executed. To perform these comparisons, one-way ANOVA or Kruskal-Wallis tests will be applied when appropriate. Subsequently, a multivariate analysis will be carried out, and the autocorrelation between repeated measures will be taken into account. We will use longitudinal analysis methods, such as a generalised estimating equation approach, to control the differences among measures at baseline and to incorporate incomplete observations into this analysis. Finally, we will investigate if there is an interaction between the two interventions for the primary outcome at 12 weeks of supervised training HIIT, RT or combined training (HIIT + RT). For these analyses, we will include appropriate interaction terms in the models [38, 65]. The trial is not powered to detect these interactions and is likely to have poor precision for the interaction terms. We plan to report regression coefficients for the interaction terms and their 95 % confidence intervals. However, we aim to recruit 15 participants per group (a total of 60) to accommodate for a 20 % attrition rate and elimination due to non-compliance.

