### Data collection and outcome measures

Outcome measures will be assessed at baseline and at 12-week follow-up by personnel blinded to the treatment allocation. Data will be recorded on standardised forms and entered into a secured-access database that contains quality control checks (e.g. range checks, notification of missing data).

The primary outcome measure is endothelial function as measured by flow-mediated dilatation (FMD). The secondary outcome variables include HR variability, pulse wave velocity (PWV), weight, BMI, WC, body composition, body temperature, biochemical profile, health-related physical fitness, self-perceived health, health-related quality of life (HRQL), and side effects. Other variables of interest include 24-hour dietary recall, lifestyle and demographic characteristics (Table 3 and Figure 3).

**Table 3 Tab3:** Summary of time point measurements of the primary and secondary outcomes of the study

Type of outcomes	Specific outcomes	Measurements		
		1-baseline (week 0)	2-moment (week 4)	3-moment (week 12)
Primary outcomes	Endothelial function as measured by flow-mediated vasodilatation	X		X
Secondary outcomes	Vascular function: heart rate variability, aortic pulse wave velocity, augmentation index and blood pressure	X		X
	Morphological component: weight, height, BMI, waist circumference	X	X	
	Body composition: fat mass and non-bone lean body mass	X		X
	Body temperature	X		X
	Plasma samples and biochemical analysis: LDL cholesterol (LDL-c), HDL cholesterol (HDL-c), total cholesterol, triglycerides, glucose, glycated haemoglobin (HbA1c)	X		X
	Fitness component: self-reported fitness, 1RM, hand-grip and peak uptake of volume of oxygen	X		X
	Self-perceived health: health-related quality of life	X		X
	Recent Physical Activity Questionnaire	X	X	X
	Demographic information	X		
	Side effects	X	X	X

*1RM* one repetition maximum, *BMI* body mass index

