#### Primary outcome measures

##### Endothelial function

FMD will be measured with the technique introduced by Ramírez-Vélez et al. [36] in the Colombian population using the guidelines reported by Corretti et al. [37]. The diameter of the brachial artery will be assessed using a high-resolution ultrasound device (Acuson Sequoia C512, Acuson Siemens, Mountain View, CA, USA), equipped with a 7.5–10-MHz linear array transducer and an integrated electrocardiography package. The ultrasound procedures will be performed with the subject resting quietly in a supine position for at least 10 min. Measurements will be performed in the morning (06.00–08.00 hours) due to diurnal variation in a climate-controlled room (18–20 °C) with the lights dimmed. All measurements will be taken at the end of diastole as observed by electrocardiogram. First, the diameter of the right brachial artery will be searched in a cross-sectional view and then scanned over a longitudinal section 5 to 10 cm proximal to the right elbow. The diameter of the brachial artery will be measured from the anterior to the posterior intima-lumen interface at a fixed distance, calculating the mean diameter from four cardiac cycles. After this, a pneumatic tourniquet placed around the right forearm will be rapidly inflated to at least 50 mmHg above the systolic blood pressure for 5 min. A sudden release of the cuff will induce an increase in blood flow in the brachial artery located proximal to the tourniquet. During reactive hyperaemia, shear stress will increase, causing endothelium-dependent vasodilatation, mainly due to endothelial release of nitric oxide [38, 39]. This secondary dilatation enhances and prolongs the reactive hyperaemic phase. FMD of the brachial artery will be measured 45–60 s after cuff release. The change in diameter caused by the increased flow will be calculated as the percentage change relative to the baseline measurement (FMD%). The intra-session coefficients of variation will be up to 1 % for baseline diameter. Reliability, estimated by intra-class correlation coefficients (ICC) based on four baseline measurements (*n* = 8 subjects), showed an ICC of 0.91 for the baseline diameter and 0.83 for FMD (*own date*). Images will be recorded on a DVD player for subsequent measurements by one observer blinded to the study.

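### The plan lists a test chosen after seeing the data, with no stated baseline covariate, and then a baseline-controlling model, without naming which gives the primary FMD result

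*Protocol article*

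**What the plan says.** All references are to the protocol article.

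- **Data available.** Data collection and outcome measures: "Outcome measures will be assessed at baseline and at 12-week follow-up by personnel blinded to the treatment allocation". Table 3 shows FMD at weeks 0 and 12. Randomisation follows the baseline measurements (Blinding and randomisation methods).
- **How the test is chosen.** Statistical analyses opens with an exploratory look at the frequency, range, "variability, and distribution type for each variable to use the most appropriate statistical test when comparisons will be necessary".
- **First-named comparison.** For the two measures in four groups, "a comparative analysis between these measures to establish differences will be executed", and for this "one-way ANOVA or Kruskal-Wallis tests will be applied when appropriate". No covariate, response variable or decision rule is given.
- **Second analysis.** A longitudinal method follows, with GEE as an example, "to control the differences among measures at baseline and to incorporate incomplete observations into this analysis".
- **Third analysis.** Last come models with HIIT-by-RT interaction terms, to be reported as coefficients with 95 % confidence intervals.

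The section sets an intention-to-treat population that includes participants with missing outcomes. It does not say which of these analyses yields the primary FMD result.

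**The concern.** Three choices are open for the primary outcome: the test (means or ranks), the response (week-12 value or change), and the status of the longitudinal model. Each combination answers a slightly different question. Kruskal-Wallis on its own gives no difference in FMD points.

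The options also differ in precision. ANOVA on week-12 values does not use baseline FMD. ANOVA on change uses it by subtraction, which over-corrects unless r is close to 1 and is worse than ignoring baseline when r is below 0.5. A model with baseline FMD as covariate has smaller variance than either whenever r lies strictly between 0 and 1. In a trial of 15 per arm that precision matters, and an unfixed choice leaves room to report whichever version looks best.

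**Working it through.** **Inputs.** Difference 2 FMD points, SD 2.7, two-sided alpha 0.05, two-sample t test, 12 per group for 80 % power, 15 per group recruited (Power calculation and sample size). Attrition is 15 % there and 20 % under Statistical analyses, leaving 15 × 0.85 = 12.75 or 15 × 0.80 = 12 per arm; I use 12. The documents give no baseline to week-12 correlation, so r = 0.3, 0.5 and 0.7 are assumptions.

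**The plan's own figure.** Its formula gives n = (1.96 + 0.84)² × 2 × 2.7² / 2² = 28.6, so 29 per group (30 by exact t test), not 12. With 12 per group, exact t-test power is 41 %. This is a separate problem, but it shows that precision is scarce.

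**Step 1: SD 2.7 read as the SD of FMD at each visit.**

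- Week-12 value alone: SD = 2.7.
- Change score: SD = 2.7 × √(2(1 − r)).
- Adjusted for baseline: SD = 2.7 × √(1 − r²).

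Power for one pair of arms, 12 per arm, noncentral t with 22 degrees of freedom:

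| r | Variance cut by adjustment, against week 12 alone | SD adjusted | SD change | Power, week 12 alone | Power, change | Power, adjusted |
|---|---|---|---|---|---|---|
| 0.3 | 9 % | 2.58 | 3.19 | 41 % | 31 % | 44 % |
| 0.5 | 25 % | 2.34 | 2.70 | 41 % | 41 % | 52 % |
| 0.7 | 49 % | 1.93 | 2.09 | 41 % | 61 % | 68 % |

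Charging one degree of freedom for the covariate lowers the adjusted figures by at most 0.2 percentage points.

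**Step 2: SD 2.7 read as the SD of change.** The adjusted variance is (1 + r)/2 of the change-score variance: 0.65, 0.75 and 0.85 at r = 0.3, 0.5 and 0.7. Change-score power at 12 per arm is then 41 %, and adjusted power is 58 %, 52 % and 47 %.

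**Step 3: effect of choosing after seeing the data.** Simulated under no effect, four groups of 12, normal and lognormal data: a Shapiro pretest followed by ANOVA or Kruskal-Wallis rejects about 5 % of the time, and reporting the better of the two about 6 %. If the response is free as well, the best of ANOVA or Kruskal-Wallis on week-12 values or on change rejects about 11 % (four groups of 15, normal data, r = 0.3 to 0.7).

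**The case against.** The strongest reply is that baseline control is already planned. The longitudinal step is there "to control the differences among measures at baseline and to incorporate incomplete observations into this analysis", and a GEE with baseline FMD as covariate, or with one baseline mean common to all groups, has essentially the precision of the adjusted model above. This stands. A reader might infer from the ANOVA sentence that the plan ignores baseline altogether; it does not. A reader might also argue that the GEE only reproduces the change-score contrast. That holds for complete data with a separate baseline mean per group, and the text specifies neither.

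A plain week-12 ANCOVA would also sit badly with the stated intention-to-treat set, because it drops anyone without a week-12 value. This stands too, and the fix allows for it.

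It might be said that Kruskal-Wallis cannot carry the planned interaction. The plan never asks it to: interaction terms belong to the later regression models.

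Finally, covariates and distributional rules are often left to a statistical analysis plan, which is not shown here. That excuses missing detail. It does not excuse what the article does state: a choice of test by inspection of the trial data, and several analyses with none given precedence.

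**Conclusion.** The point holds in this limited form: baseline adjustment is planned, but nothing says that it governs the primary FMD result, and the comparison named first is chosen from the data with its response unfixed.

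The gain from fixing it runs from small to substantial: 3 points of pairwise power at r = 0.3, 27 points at r = 0.7, against a week-12-only comparison at 12 per arm. Against change scores at r = 0.3 it is 13 points (44 % against 31 %). These figures rest on the assumed r and on how SD 2.7 is read.

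Two stronger readings are not supported. The protocol reports that repeated measurements in 8 subjects "showed an ICC of 0.91 for the baseline diameter and 0.83 for FMD". Using 0.83 as r would give much larger gains, but it is repeatability at baseline, at best an upper bound for the 12-week correlation. Nor does the material show serious type I error inflation from the choice between ANOVA and Kruskal-Wallis alone. The 11 % figure measures the room that the wording leaves, not how the trial will be analysed. Adjustment also does not rescue the sample size: 12 per group reaches 80 % power only if r is about 0.76, from √(1 − 12/28.6).

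**What to change.** Name one primary analysis before the data are examined: a linear model of week-12 FMD% with baseline FMD% as covariate and the randomised groups as terms, or the equivalent longitudinal model with a common baseline mean. The second form keeps participants without a week-12 value in the intention-to-treat set, although with two visits they add little information and the result still rests on an assumption about why values are missing. Report adjusted differences in FMD points with 95 % confidence intervals.

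Do not select the test by distribution. If residuals are skewed, keep the model and use robust standard errors or a permutation p-value. Label ANOVA and Kruskal-Wallis as descriptive, or delete them.

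The cost is one degree of freedom and a sentence in the analysis plan. Baseline FMD is already measured before randomisation, so no extra data are needed.
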